Questionnaires	Measure outcomes and need to be filled out before accessing the elements behind login. Questionnaires will be activated in the personal menu. Questionnaires can be filled out one-by-one. Whenever possible, adaptive questioning is being used to make the burden as low as possible. There is a maximum of 15 questions per page. All items need to be filled out to submit a questionnaire. Participants cannot review their answers.	Available after first login, re-activated after 6,12, 18 and 24 weeks. *Element will no longer be obligated after trial.*
Personal menu	Menu for the participants with overview to all the available elements, access to the participants profile, digital testament, research information and contact information.	Login needed
User profile	The profile contains information on the participant, being: full name, nickname, avatar, sex, age, contact details and contact person. Only the nickname is available for other participants. The participant can choose a theme for the lay-out.	Login needed
Digital testament	The digital testament is required to fill out and lets participants choose how their data must be handled if they stop their participation.	Login needed
Ask the expert	Option to ask questions by e-mail to several experts, including a general practitioner, a sexologist, a psychologist and an expert in the field of family violence. Participants can also contact the community manager for general questions and questions regarding regular healthcare services. Response is given within 72 hours. During the RCT, this is the only available element for participants in the control group.	Login needed & questionnaires finished
Forum	The forum is meant to stimulate peer support. The community manager moderates the forum and stimulates contact. She will not intervene in the conversations except in case of offensive or factually wrong comments.	Login needed & questionnaires finished
Chat	Every two weeks we will offer a chat session for the participants with a specific theme and supported by an expert. Every other week there will be an unguided chat.	Login needed & questionnaires finished
Information	Information will be offered to the participants. Depending on the age in the profile, participants have access to tailored information about partner violence, sexual health, reproductive health, relations and healthcare. Participants are encouraged to discuss topics on the forum.	Login needed & questionnaires finished

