**Figure 1 F1:**
[figure not shown]
**Flowchart randomization procedure, received care and data collection.** Abbreviations: mEUC = minimally enhanced usual care, UC = usual care.

The intervention group will receive immediate access to “Feel the ViBe” after registration. Considering ethical concerns of withholding an intervention with a possible positive effect on physical and mental health, the control group will be a waiting list condition receiving minimally Enhanced Usual Care (mEUC) for twelve weeks before getting access to the intervention. mEUC is in general defined as non-study care enhanced in minor ways to address methodological or ethical issues. For this RCT mEUC is defined as Usual Care and access to a restricted version of “Feel the ViBe” offering only access to the user profile, consent forms, digital testament, research information, questionnaires and the “ask the expert” function to ask questions in case of emergency. Questions asked by members of the control group will not be answered by the Community Manager, but by one of the members of the Research Team who is not actively involved in the intervention, being author [name]. If help is needed immediately, the participant will be referred to his/her GP (Figure 1).

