### Data analysis

Data will be collected for the duration of one year.

First, descriptive statistics of the characteristics of the intervention and the control group will be compared to check whether randomization resulted in similar groups.

The effectiveness of the intervention will be tested with ANOVA of the primary outcome measures. This gives us the opportunity to compare not only the intervention with mEUC (between groups effects), but also to do pre-posttest analysis for all participants (within subjects effects). Data will be analyzed in SPSS. Effect sizes will be expressed in Cohen’s *d* to make data comparable with earlier studies. Data will be analyzed both together and separately for the group 12–17 years old and 18–25 years old.

In e-health trials attrition is typically high and not all participants will use the intervention as intended. A participant will be excluded from analysis if he/she visited the intervention less than five times. His/her entry data (t = 0) will be used to describe baseline characteristics [56].

To interpret the findings, usage data, the WEQ, and the interviews held with the participants after finishing their participation will be analyzed alongside. Qualitative data will be analyzed with qualitative coding [57]. Interview data will be recorded and transcribed. Two researchers will study all transcripts independently, identify themes and establish the definite codes. Consensus will be reached in mutual discussion. Subsequently these outcomes will be formulated and interpreted in the supervising research group for final results. Quotes will be used to underline the results.

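### The five-visit exclusion selects the effectiveness comparison on behaviour that follows randomisation and depends on allocation, and it does not define a visit

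*Protocol article*

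**What the plan says.** Under Data analysis, the test of effectiveness is set out in one sentence: "The effectiveness of the intervention will be tested with ANOVA of the primary outcome measures". The text then explains that this covers both a between-group comparison of the intervention with mEUC and a within-subject comparison over time.

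The same section gives a reason for restricting the analysis, "In e-health trials attrition is typically high and not all participants will use the intervention as intended", and then the rule: "A participant will be excluded from analysis if he/she visited the intervention less than five times". What remains of an excluded person is limited: "His/her entry data (t = 0) will be used to describe baseline characteristics". The rule is not labelled per-protocol, supplementary or sensitivity.

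The Intervention section describes access by arm. For one arm, "The intervention group will receive immediate access to" the website after registration. For the other, "the control group will be a waiting list condition receiving minimally Enhanced Usual Care (mEUC) for twelve weeks before getting access to the intervention". Until then controls log in to a restricted version with profile, consent forms, digital testament, research information, questionnaires and the ask-the-expert function. Table 1 says of that last function: "During the RCT, this is the only available element for participants in the control group".

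**The concern.** Randomisation makes the two groups comparable on everything that precedes allocation. That protection is lost once people are removed on something that happens later and differs by arm. The number of visits is such a quantity: what there is to visit depends on allocation, and how often someone returns may depend on how they are doing.

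The article itself gives reason to expect a link between visiting and outcome. Use is as desired, with no prescribed number of visits. One aim of the website is to lower the threshold to existing healthcare, and the article expects a minority to need face-to-face help. A person who visits twice and then goes to a professional could be a success or a treatment failure, but either way is dropped.

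The rule is also more than a way of handling missing outcomes. Under Table 1 the questionnaires open at first login and again at weeks 6 and 12. Someone could complete all three rounds in three logins and still be discarded with full data to week 12.

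At stake is the only effectiveness test that the article describes.

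**Working it through.** **Step 1. Can the rule be applied without breaking the randomised comparison?** The article does not define a visit, the arm concerned or the counting period. Three readings are open:

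| Reading | Intervention arm analysed | Control arm analysed | Consequence |
|---|---|---|---|
| Rule applies to the intervention arm only | Those with five or more visits | Everyone | Selected users against unselected controls |
| Logins to the restricted site count for controls | Five or more visits to the full site | Five or more logins to a site with little on it | The threshold measures a different behaviour in each arm |
| Controls' visits after week 12 count | Five or more visits from the start | Five or more visits after the waiting period | Controls are selected on behaviour that follows the week-12 comparison and may depend on its result |

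In each row people leave the analysis after randomisation for reasons that allocation affects.

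**Step 2. The plan's own figures.** The article gives no expected share of low users and no relation between use and outcome, so there is no stated figure to reproduce for this point. The only related number taken from the plan is the target of 50 per group (Sample size).

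**Step 3. Illustration of size.** Assumptions, none of them from the documents: no true effect; first reading; a share q of the intervention arm excluded; all 50 controls kept; outcome is a standardised follow-up score; correlation ρ between propensity to visit and outcome, both normal.

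Bias in SD units = ρ × φ(c) / (1 − q), where c is the q-quantile of the standard normal distribution.

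For q = 0.4 and ρ = 0.3: c = −0.253, φ(c) = 0.386, so bias = 0.3 × 0.386 / 0.6 = 0.193.

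The standard error with 30 against 50 is about √(1/30 + 1/50) = 0.231. The shift is 0.193 / 0.231 = 0.84 standard errors. The chance of a two-sided 5% rejection is Φ(0.84 − 1.96) + Φ(−0.84 − 1.96) ≈ 0.131 + 0.003 ≈ 13%. A simulation of 20,000 trials gave 13.4%.

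The same simulation over a range (bias in SD; two-sided error at nominal 5%):

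| ρ | 20% excluded | 40% excluded | 60% excluded |
|---|---|---|---|
| 0.1 | 0.04; 5.3% | 0.06; 5.7% | 0.10; 6.4% |
| 0.3 | 0.11; 7.6% | 0.19; 13.4% | 0.29; 18.9% |
| 0.5 | 0.18; 13.2% | 0.32; 28.9% | 0.48; 44.9% |

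The sign of ρ is unknown, so the bias may favour or disfavour the intervention. At ρ = 0 there is none.

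**Step 4. If change from baseline is analysed.** Write ρ₀ and ρ₁ for the correlations of visiting with the baseline and follow-up scores, each with SD 1. The bias in mean change is then (ρ₁ − ρ₀) × φ(c) / (1 − q). If the two correlations are equal it is zero. For a change-score or group-by-time contrast, what matters is whether visiting is related to change.

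**Step 5. Power.** With 50 per group, d = 0.7 and a two-sided 5% test, power is 93.8%. Removing 20% or 40% of the intervention arm (40 or 30 against 50) leaves 91.0% or 85.8%. Loss of power is a minor part of the problem.

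**The case against.** The strongest reply is that the article is a condensed protocol and an all-randomised analysis may stand in a fuller document. That is possible. However, the point rests on a positive, unqualified sentence in the article, not on something left out of it.

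Several stronger readings are tempting but not supported:

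- **Only the intervention arm can record visits.** Controls log in to a restricted version before week 12 and have full access afterwards.
- **Taken literally, the rule removes every control at weeks 6 and 12.** The rule sets no time window. A control who visits often enough after week 12 meets it.
- **The plan has no comparison by allocated arm.** It has one, intervention against mEUC. What is at fault is the set of people who enter it.
- **The baseline table would hide imbalance.** The article says only that excluded people's entry data help to describe baseline characteristics. It does not rule out a table of the analysed set.

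It is also fair to say that the illustration takes one reading and one type of contrast. The planned ANOVA includes within-subject effects and the outcomes are measured at baseline, so the error in the actual analysis could be smaller than the table shows. A low correlation would leave it near nominal. These objections limit what can be said about size. They do not restore the randomised comparison under any reading.

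**Conclusion.** The concern holds in this form: an undefined exclusion after randomisation governs the only effectiveness comparison described, and it can bias that comparison in either direction. It should be corrected before the analysis. The size cannot be derived from the documents. The figure of 0.19 SD and about 13% error rests on an assumed 40% exclusion, an assumed correlation of 0.3, a comparison of follow-up scores, all controls kept and no true effect. It shows that the bias can matter and is not a forecast. The lack of definition adds to the problem, because the choice among readings could be made after data are seen, and the Randomization section explains that blinding the investigators is difficult.

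**What to change.** Replace the exclusion sentence with three statements.

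1. The primary comparison of the intervention with mEUC, up to week 12, includes all randomised, consenting participants in their allocated arm, whatever their number of visits. The one exception is people found to be outside the target group, whose data the Exclusion criteria section already sets aside. That decision should rest on eligibility alone and be applied alike in both arms, since greater contact with the intervention arm could otherwise reveal more ineligible people there.
2. All available outcome data are used with a stated missing-data method, for example a likelihood-based mixed model for the repeated measures including baseline. This is needed because questionnaires are completed behind the login, so many low users may lack follow-up.
3. The five-visit set is kept as a supplementary per-protocol analysis, labelled as such, with a definition of a visit, the arm and the counting period.

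A complier-average analysis with five visits as the threshold is not a good substitute. One to four visits, and the daily facts sent by e-mail or mobile, may have effects of their own, so the assumption that allocation does not affect people below the threshold is doubtful.

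The cost is a few sentences and somewhat more analysis work, with no new data collection. The estimate will probably be smaller, because low users are included.

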### Ethical and safety issues

The Committee on Research Involving Human Subjects of the Radboud University Nijmegen Medical Centre (Dutch initials: CMO) has assessed this study and judged that the study does not fall within the remit of the Medical Research Involving Human Subjects Act (WMO). Therefore, the study can be carried out (in the Netherlands) without approval by an accredited research ethics committee (2011/053. NL nr 35813.091.11. March, 16th, 2012).

After signing up, all participants receive a username and password to create security and to follow them for analyzing properties. Each participant will receive a number. We hereby secure the anonymity of adolescents. To enhance the safety even more, the website is based on a secured server, which meets the safety criteria for e-health applications containing medical information. Acquired data will be handled according to the digital testament of the participant. Quantitative data will be collected during the trial on a secured server. The community manager moderates the interactive parts of the website and, if applicable, asks participants to remove personal information.

Participants can email or call the community manager, even if they have not completed the obligated parts. Emails are answered within 72 hours. If there are concerns, for the safety of a participant or his/her close family, the participant will be addressed by the community manager to discuss this further. All participants are asked to give contact details of an adult they trust. In case of severe danger, the community manager can contact this person with consent of the participant, or, if a participant is below 16, also without consent. The participant is free to decide whether he/she continues with Feel the ViBe.

## Discussion

This study protocol describes the process of developing and evaluating an internet-based self-support method “Feel the ViBe” for children, adolescents and young adults exposed to family violence.

E-health research is still relatively new and has some limitations due to its online nature: attrition is usually high which makes sample size calculations difficult. Data must be handled differently than offline data, because safety and privacy issues are a concern, especially in our target group. While making this protocol, the authors followed the CONSORT-EHEALTH checklist version 1.6.1 and The Checklist for Reporting Results of Internet E-surveys (CHERRIES) [58-61].

Publishing a research protocol before starting a RCT is essential. It not only prevents publication of positive-only results, by changing the protocol or outcome-measures, it also enables researchers to discuss their intervention and methods more in-depth. There are some limitations to this study: developing an online intervention for a vulnerable group of adolescents means it is hard to reach a representative sample. For this RCT, participants will register themselves, which means only participants actively searching for help and having access to the internet will be included. However, in the Netherlands, 93% of children above twelve years old have access to the internet and the researchers try to further minimize this bias by advertising the intervention in a broad way, both online and offline [32,33]. To keep attrition to a minimum, researchers send reminders for questionnaires and daily “facts and figures” to the participants. A process evaluation is being held to investigate, amongst others, recruitment and attrition. Lastly, the community manager monitors the intervention to motivate participants to be actively involved. To minimize possible bias, all actions of the external community manager will be registered and discussed with the supervising research team. Results of the questionnaires will be collected during the trial and delivered to the researchers at the end of the trial. In this way, the community manager cannot be influenced by questionnaire results.

“Feel the ViBe” is not the first intervention for this target group. However, “Feel the ViBe” is an online-only intervention, it offers help to older children, adolescents and young adults and is self-supporting. The intervention “Feel the ViBe” is developed in close collaboration with the target group. A RCT and a process evaluation will follow to test effectiveness and help us understand how the effects of the intervention can be explained, how the interventions meet the expectation of the participants and what possible barriers and facilitators for implementation are. Qualitative analysis will complete quantitative data. This makes “Feel the ViBe” unique in its field.

## Abbreviations

Feel the ViBe: Feel the violence beaten; UC: Usual care; mEUC: minimally Enhanced Usual Care; WEQ: Web evaluation questionnaire; PTSD: Post traumatic stress disorder; STD: Sexually transmitted disease; IES: Impact of event scale; SCL-90-R DEP: Symptom checkList-90-R, depression subscale; SCL-90-R ANX: Symptom checkList-90-R, anxiety subscale; ROM: Routine outcome monitoring; CHERRIES: The CHEcklist for reporting results of internet E-surveys.

